#### Intervention

Each session will present, discuss and enact a certain parenting practice (Table 1). The Play & Grow will have educational strategies including instructions, parental peer support and group discussions, and homework tasks, in accordance with the elements developed in our Play & Grow pilot study. Each session will comprise: (i) 15 min of guided active play involving both children and parents; (ii) 15 min of interactive education and skill development for parents; simultaneous supervised active play with foods for children, to promote acceptance of vegetables, and (iii) 15 min of guided active nature games outdoors, involving both children and parents. The sessions will incorporate a lifestyle component, for example: eating, active play and connectedness to nature). These will target the parents’ knowledge and skills on how to introduce and maintain their child’s correct lifestyle routines. A group leader and co-leader with healthcare backgrounds (and trained by the PI during the Play & Grow pilot study) will facilitate the sessions involving 4 to 5 parent-child dyads.

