#### Participants and randomization

Two to four year old children and their English-speaking parents will be recruited through kindergarten advertisements and via the HKU website. For continuity of delivered message, both parents in two-parent families will be invited to join. According to our pilot experience, however, we expect mostly mothers and domestic helpers to attend. The fathers will be welcome as well, but the same caregiver should fill the questionnaires. We set up a requirement of 80 % participation attendance of the same caregiver. Given the Play & Grow pilot data, 100 children in each group (*p* < 0.05 and power 0.8) will be needed to detect changes between the intervention and control groups. The WLCG children will be offered the Play & Grow programme at study completion (Fig. 3).

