#### Power and sample size

The primary outcomes for this intervention relate to eating, active play and Connectedness to nature habits. The sample size calculation is based on a similar study conducted in New Zealand, MEND 2–4, which provides relevant parameter estimates for children aged 2 to 4 years of age [35, 36]. As there have been no similar interventions in this age group in Hong Kong, we adpoted the MEND design suggestion and calculated the sample size first of all, in regards to our primary outcomes (for example, 25 % increase in vegetable consumption), hence 100 families in each group will be required for a power of 0.8, α = 0.05 [35]. Based on the pilot data, and the dropout rate of 20 %, we intend to recruit 240 families. This sample size will be sufficient to detect medium effect sizes (power of 0.8 at α = 0.05) in our the secondary outcomes [37]. To increase retention in the study, we will build connections with the participants through a blog created for the Play & Grow pilot, and send birthday cards to each child participant.

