#### Analysis

To describe the demographic and other subject characteristics and to evaluate the distributions the descriptive statistics will be applied. We will use an intention-to-treat statistical approach. Regression models will address the effect of the intervention on the studied outcomes (Multivariate Analysis of Variance, multiple regressions, controlling for baseline and other covariates). Linear mixed modelling will be used to analyse physical activity/sedentary behaviour changes, dietary habits, zBMI and food neophobia. Our sample should be adequate for running a two-way (2x3) repeated measures ANOVA for our study, but if the sample is not normally distributed, a non-parametric two-way ANOVA, namely the adjusted rank transform ANOVA, to analyse the between-subject effect, within-subject effect, and interactions effects will be used [54].

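### Small-group delivery in one arm is not reflected in the independence-assuming analyses that the protocol names, nor visibly in its sample size

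*Protocol article*

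**What the plan says.** **Design and delivery.** Under STAGE 2, families are randomised individually to the programme or to a waiting list. The Intervention section states that the leader and co-leader "will facilitate the sessions involving 4 to 5 parent-child dyads" and lists "parental peer support and group discussions" among the educational strategies. The abstract gives ten weekly sessions, and Table 1 runs from a welcome session to a graduation. Participants and randomization says that waiting-list families receive the programme only after the study ends.

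**Sample size.** Power and sample size states that "100 families in each group will be required for a power of 0.8" at α = 0.05, "in regards to our primary outcomes (for example, 25 % increase in vegetable consumption"). The source is given as follows: "The sample size calculation is based on a similar study conducted in New Zealand, MEND 2–4, which provides relevant parameter estimates". Participants and randomization gives the same number with a different basis: "Given the Play & Grow pilot data, 100 children in each group". Neither section mentions an ICC, a design effect or the size of the session groups.

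**Analysis.** The RCT Analysis section says "Regression models will address the effect of the intervention on the studied outcomes" and names MANOVA and multiple regression with baseline and other covariates. It assigns linear mixed modelling to activity and sedentary behaviour, diet, zBMI and food neophobia. It then proposes a 2x3 repeated-measures ANOVA, or a rank-transform version if the data are not normal. Session group appears in none of these. Connectedness to nature, listed as primary in Power and sample size, is not among the outcomes assigned to the mixed model.

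**The concern.** Families who meet in the same small group share leaders, discussion, activities and peers, and this sharing is a deliberate part of the treatment. Their outcomes are therefore likely to be positively correlated within a group. Waiting-list families have no such grouping, so the correlation arises in one arm only.

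A test that treats all families as independent then uses too small a standard error for the difference between arms. Confidence intervals are too narrow, and the test favours declaring the programme effective. More families do not cure this, because the error lies in the variance estimate. If the sample size was also computed for independent families, the stated power for the primary outcomes is somewhat too high.

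One practical matter is time-critical. If nobody records who sat in which group, the correct analysis may not be possible later.

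**Working it through.** **Inputs from the protocol:** 100 per arm, power 0.8, α = 0.05 (two-sided assumed), groups of 4 to 5 (midpoint m = 4.5). For 100 intervention families this means 100/5 = 20 to 100/4 = 25 groups.

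**Assumed:** the ICC, which the protocol does not give, taken as 0.02, 0.05 and 0.10; equal total variance in both arms, set to 1; stable groups.

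**1. The plan's own figure.** The 100 per group can be neither reproduced nor refuted, because no mean, SD or rate is printed. Under independence it corresponds to a standardised difference of d = (1.960 + 0.842) × √(2/100) = 0.396, which is used below as the primary-outcome effect.

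**2. Formulas.**
- Design effect, intervention arm only: DE = 1 + (m − 1) × ICC. In the control arm it is 1.
- True SE of the difference: √((DE + 1)/n). Ratio to the unadjusted SE: R = √((DE + 1)/2).
- Type I error of the unadjusted test: 2 × (1 − Φ(1.96/R)).
- Power with the correct SE: Φ(d/SE − 1.96).

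**3. Worked case, ICC 0.05.** DE = 1 + 3.5 × 0.05 = 1.175. R = √(2.175/2) = 1.043. Type I error = 2 × (1 − Φ(1.96/1.043)) = 0.060. SE = √(2.175/100) = 0.1475. Power = Φ(0.396/0.1475 − 1.96) = 0.766.

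**4. Results (100 per arm, m = 4.5).**

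| ICC (assumed) | DE | R | Type I error, unadjusted | Power, d = 0.396 | Power, d = 0.5 |
|---|---|---|---|---|---|
| 0.02 | 1.07 | 1.017 | 0.054 | 0.786 | 0.935 |
| 0.05 | 1.175 | 1.043 | 0.060 | 0.766 | 0.924 |
| 0.10 | 1.35 | 1.084 | 0.071 | 0.734 | 0.903 |

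With d = 0.398 instead of 0.396, the primary-outcome powers round to 0.79, 0.77 and 0.74, so the last is best read as 0.73 to 0.74.

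**5. Sensitivity to group size.** At ICC 0.05, power is 0.771 for m = 4 and 0.762 for m = 5. At ICC 0.10 it is 0.743 and 0.725.

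**6. Check by simulation.** With 20 groups of 5 against 100 independent controls (20,000 runs), the unadjusted t-test rejected a true null in 0.060 of runs at ICC 0.05 and 0.073 at ICC 0.10. The formula for m = 5 gives 0.062 and 0.074.

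**7. Secondary outcomes.** For a medium effect, taken by convention as d = 0.5, power remains 0.848 even at ICC 0.20 with m = 5. The protocol's 0.8 for those outcomes stands.

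**The case against.** A reader might infer that every named analysis treats families as independent. The document does not show this. The linear mixed model is named without its random effects, so it may be meant to include session group, and an article can leave that detail to an analysis plan. It covers two of the three primary domains, eating and activity. This point stands. It does not remove the concern: MANOVA, multiple regression and the ANOVAs are positive choices with no group term, the ANOVA is proposed for the study as a whole, and they are the only methods left for Connectedness to nature.

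A reader might also infer that the sample size certainly assumed independence. The text is silent, and the figure is taken from an outside study whose inputs are not printed. The loss of power is therefore conditional.

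Stable groups are implied by the ten-session sequence but not stated. The attendance rule concerns the same caregiver, not the same group. If one leader pair served every group, leaders would add no variation between groups, but peer discussion still could.

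The size is modest at low ICC. Baseline adjustment may also recover power if it was not already counted in the 100. An assumed baseline correlation of 0.3 multiplies the variance by 1 − 0.09 = 0.91. Against the average inflation of (1.175 + 1)/2 = 1.0875 at ICC 0.05, this gives 0.99, roughly a full offset. That helps power but does nothing for the type I error of an unadjusted test.

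**Conclusion.** The concern holds in a limited form. Group delivery in one arm is stated, and the named MANOVA, regression and ANOVA methods do not account for it. For any positive ICC with stable groups, their standard errors are too small. Over an assumed ICC of 0.02 to 0.10, the type I error of an unadjusted test is about 0.054 to 0.071.

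If the 100 per group assumed independence, primary-outcome power falls from 0.80 to between about 0.79 and 0.73 to 0.74. The direction does not depend on the ICC chosen; the size does.

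Three stronger readings are not supported: that the mixed model lacks a group term, that the sample size is known to ignore clustering, and that the 0.8 for medium secondary effects is overstated. The allowance for dropout is a separate matter and plays no part in these figures.

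**What to change.** 1. State whether session groups are fixed for the ten weeks, and record the group identifier at each session, so that any movement between groups is known.
2. For all continuous RCT outcomes, including Connectedness to nature, make the linear mixed model already named the inferential analysis, in place of MANOVA and the ANOVAs. Add a session-group random effect in the intervention arm only, with each control family as its own singleton, a residual variance for each arm, and Satterthwaite or Kenward-Roger degrees of freedom. If families change groups, the group term must follow actual membership.
3. State whether the 100 per group already allows for group clustering. If it does not, restate primary-outcome power over a stated ICC range, for example 0.02 to 0.10, using the one-arm design effect. The target of 240 families need not change for this.

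The cost is one variable recorded at delivery and one added variance structure in a model already planned. Intervals become slightly wider and the stated power for the primary outcomes slightly lower.

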#### The novel Connectedness to nature element

The most appropriate way of instilling habits related to nature is to stimulate children's natural curiosity as early in life as possible. This could be done by involving caregivers and educating them about nature-related activities [30, 38–41]. In adults, research demonstrates a correlation between learning about the nature and the length of time spent in nature [42]. Connectedness to nature is described as including basic environmental knowledge, environmental sensitivity and awareness, as well as a commitment to protect nature [28]. In the proposed intervention, we will employ environmental education and nature-related activities to help participating families develop skills conducive to improving playtime and eating habits in children. Examples of the additional elements that make up an 1/3 of the programme are: i) inclusion of active nature games outdoors that involve both children and parents focusing on motor skills, discovering nature, practicing awareness to sounds, touch, smells, temperature, ii) group activities with other families and members, practicing nature related activities, iii) nature homework with follow-ups (collect objects found in nature and make art or grow their own plants), iv) environmental care training (paper waste, water saving, recycling), and v) studying new vegetables and cooking together with them (avocado, using the avocado to make a boat, turning the avocado into guacamole, etc.).

### Primary outcomes and their assessments

Measurements will be conducted prior to and after the 10-week intervention, with further follow up assessments at 6 and 12 months in order to observe both the short and long term outcomes (Table 2). Although many variables will be measured in both children and participating parents, we carefully chose a few questionnaires, which covered multiple variables.

**Table 2 Tab2:** Intervention outcome instruments

Intervention Outcomes	Source	Baseline	End-of-intervention	6-month Follow-up	12-month Follow-up
Parent					
General Parenting Practices					
Knowledge of children’s:					
Feeding	PCFQ	✕	✕		
Nutrition	NKQ	✕	✕		
Active play	Pre-PAQ	✕	✕		
Connectedness to nature	NRS (self-developed)	✕	✕		
Correct practices:					
Feeding	CFPQ	✕	✕	✕	✕
Nutrition	NKQ	✕	✕	✕	✕
Active play	Pre-PAQ				
Connectedness to nature	NRS (self-developed)	✕	✕	✕	✕
Parental self-efficacy for correct practices	INFANT scale	✕	✕	✕	✕
Parental modelling of healthy habits, diet, active play, connectedness to nature	INFANT scale	✕	✕	✕	✕
Limit setting	Self-developed scale	✕	✕	✕	✕
Specific Parenting Practices					
Diet	CEBQ	✕	✕	✕	✕
Active Play	IPAQ, Pre-PAQ	✕	✕	✕	✕
Sedentary time	Pre-PAQ	✕	✕	✕	✕
Connectedness to nature	NRS (self-developed)	✕	✕	✕	✕
Child					
Eating Habits	EPAQ	✕	✕	✕	✕
Physical Activity	Pre-PAQ	✕	✕	✕	✕
Sedentary Behaviour	Pre-PAQ	✕	✕	✕	✕
Food Neophobia	PCNS	✕	✕	✕	✕
Connectedness to nature	NRS (self-developed)	✕	✕	✕	✕

Please see detailed references in proposal’s text

#### Eating habits

A short validated Eating and Physical Activity Questionnaire (EPAQ) will be used [43] and The Children’s Eating Behaviour Questionnaire (CEBQ), previously validated by the PI in China [44], will be used to assess the children's eating styles/habits.

#### Physical activity and sedentary time

Physical Activity Questionnaire for Preschool-aged Children (Pre-PAQ®) [45] valid for young children’s activity habits [46].

#### Nature relatedness

Connectedness to nature in children will be measured using a short, age-adjusted NRS scale that will be validated in Stage 1. The scale uses a number of specific questions about environmental sensitivity, distance from home to natural areas, how often and how long the family spends in nature and what nature-related activities are done, including questions on recycling, garbage sorting and saving water.

### Secondary outcomes and assessments

Many of the MENT study assessments will be used in this RCT, since they are validated for this age and outcomes [46]. These include *Parental knowledge of nutrition* (Nutrition Knowledge Questionnaire (NKQ) [47]), *Parental behaviours related to feeding, eating and physical activity* (The Preschool Child Feeding Questionnaire (PCFQ) [48] and the Child Feeding Questionnaire (CFQ) [8]); Validated Active Australia Survey [49]; Parental encouragement and parent cognitions: 5-point Likert scales, Pliner’s Child Neophobia Scale (PCNS) [50].

#### Anthropometry

Anthropometric data will be collected and aggregated according to the standard techniques and age-adjusted references [36, 51]. The Body Mass Index (BMI, kg/m2) will be calculated for each participant, BMI-for-age z-scores will be used to for children, following the WHO recommendations for children by age and gender [52, 53]. Parental age, socioeconomic status and education level will be assessed according to the study protocols developed for Hong Kong and tested during the Play & Grow pilot project.

#### Analysis

To describe the demographic and other subject characteristics and to evaluate the distributions the descriptive statistics will be applied. We will use an intention-to-treat statistical approach. Regression models will address the effect of the intervention on the studied outcomes (Multivariate Analysis of Variance, multiple regressions, controlling for baseline and other covariates). Linear mixed modelling will be used to analyse physical activity/sedentary behaviour changes, dietary habits, zBMI and food neophobia. Our sample should be adequate for running a two-way (2x3) repeated measures ANOVA for our study, but if the sample is not normally distributed, a non-parametric two-way ANOVA, namely the adjusted rank transform ANOVA, to analyse the between-subject effect, within-subject effect, and interactions effects will be used [54].

## Discussion and potential implications

Firstly, this study will develop, test and validate in Hong Kong an instrument to measure Connectedness to nature in preschool children in Hong Kong. This scale could be the first promising tool for understanding and predicting health-related environmental attitudes and behaviours, and how these change over time. It has the potential to be used for establishing causal associations between an intervention and an outcome and evaluation of health-promoting interventions in general.

To the best of our knowledge, this type of intervention is novel in Hong Kong and internationally. The results are expected to contribute to the knowledge on physical activity and diet in preschool children and by introducing a new environmental element, Connectedness to nature, to the healthy lifestyle recommendations.

## Abbreviations

AGF, anticipatory guidance framework; BMI, body mass index; CFQ, child feeding questionnaire; IG, intervention group; INFANT, infant feeding activity and nutrition trial; MANOVA, multivariate analysis of variance; NKQ, nutrition knowledge questionnaire; NRS, nature relatedness scale; PCFQ, the preschool child feeding questionnaire; PCNS, Pliner’s child neophobia scale; RCT, randomised controlled trial; WLCG, waiting-list control group.
